### Safety analysis

All data will be collected by data collectors, consisting of two nursing undergraduates. Any treatment-related adverse events (AEs), such as allergies, fainting, vomiting, prolonged skin numbness, redness, swelling, pain, or other injuries occurring within 24 h after each treatment, will be closely monitored and documented. These observations will be made either through direct observation by interveners or through self-reports by the patients (14). During the intervention process, if the occurrence of AEs exceeds 5%, we will hold discussions and make appropriate adjustments to the research protocol. Once identified, all AEs related to treatment will be covered by the research group.

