### Intervention

The control group will receive standard perioperative care, which includes preoperative health education, an optimized anesthesia plan, intraoperative heat preservation measures, and minimized surgical trauma.

The intervention groups and the sham intervention group will undergo transcutaneous electrical acupoint stimulation (TEAS) in addition to the standard perioperative care provided to the control group. Specifically, electrodes will be attached to the skin surface of the acupoint and connected to the transcutaneous electrical stimulators (SDZ-III, Suzhou Medical Technology, Suzhou, China). The device will operate at a frequency of 2/100 Hz, utilizing disperse-dense waveforms. The stimulation intensity will be adjusted to a level that the patient can tolerate, but will not exceed 10 mA. The output will consist of an asymmetrical biphasic pulse wave, with a pulse width of 0.2 ms ± 30% (based on electromagnetic compatibility basic performance testing).

Considering the specificities of gastrointestinal organs and the principles of “Xingnao Kaiqiao Acupuncture” in traditional Chinese medicine (22), two acupuncture points have been selected: bilateral Neiguan (PC6) and Zusanli (ST36). Traditional Chinese medicine posits that gastrointestinal surgeries, like those causing physical trauma, may lead to essence deficiency, loss of “Qi, “stagnation, and blood stasis. Therefore, postoperative recovery should focus on eliminating blood stasis, promoting collateral circulation, and restoring visceral “Qi” (23).

PC6 is located on the inner side of the forearm, approximately 3 cm proximal to the transverse carpal crease, positioned between the palmaris longus tendon and the radial flexor carpi tendon (24). PC6 is an acupoint on the Pericardium Meridian of Hand Jueyin and is closely related to mental activities, cognitive function, and brain function (25). ST36 is located 3 inches below the outer side of the knee (26). ST36 is considered one of the primary acupoints on the Stomach Meridian of Foot Yangming and is associated with functions such as regulating the spleen and stomach, tonifying the middle, replenishing Qi, and promoting meridian flow (27). Please refer to Figure 2 for the precise location of these acupoints. During TEAS treatment, the acupoints on the same side will be grouped together for stimulation.

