**Figure 2 fig2:**
[figure not shown]
Location of acupoints.

The timing of TEAS treatments for each group were as follows:Preoperative TEAS group: 30 min before anesthesia (28).Intraoperative TEAS group: From 30 min before anesthesia to the end of surgery (29).Postoperative TEAS group: For 7 consecutive days after the operation, once daily in the morning, with each session lasting 30 min (30).Pre-and postoperative TEAS group: From 1 day before the operation until 7 days after, once daily in the morning, with each session lasting 30 min (30).Perioperative TEAS group: 30 min before anesthesia until the end of surgery, 1 day before the operation, and on the 1st, 2nd, and 3rd days after surgery in the morning, each session lasting 30 min (14).Sham TEAS group: Electrodes will be placed in the same manner as the perioperative TEAS group but without electrical stimulation. Participants will be informed that the treatment has no sensation.

Two nursing postgraduates, who will serve as interveners, are required to spend 2 months in the Traditional Chinese Medicine Department of the hospital, dedicating 4 h each day to learning the functions and locations of acupoints, as well as the inspection and use of the instruments. To be eligible to participate in this intervention, the interveners must successfully pass a final examination, which will assess both theoretical knowledge and practical skills, administered by the Traditional Chinese Medicine Department.

During the experiment, a specialist from the Chinese Medicine Department will be invited to assess the appropriateness of acupoint selection and treatment intensity on a weekly basis. If any inaccuracies are identified in either the acupoint selection or treatment intensity, the intervener will be required to rejoin the Traditional Chinese Medicine Department for further training until they can accurately locate the acupoints and determine the correct treatment intensity. If a patient is affected by any such inaccuracies, they will be required to withdraw from the study.

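### Adverse events are captured per treatment session, so the arms are observed for 0 to 8-9 windows and their event percentages are not comparable across schedules

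*Protocol article*

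**What the plan says.** The Safety analysis section of the protocol article defines what is recorded: "Any treatment-related adverse events (AEs), such as allergies, fainting, vomiting, prolonged skin numbness, redness, swelling, pain, or other injuries", with the time limit "occurring within 24 h after each treatment". Events come to notice "either through direct observation by interveners or through self-reports by the patients". No other observation period for adverse events is stated. The same section adds an action rule: "if the occurrence of AEs exceeds 5%, we will hold discussions and make appropriate adjustments to the research protocol".

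The number of treatments differs by design. In the Intervention section, "The control group will receive standard perioperative care" and no TEAS sessions. The timing list in that section includes "Preoperative TEAS group: 30 min before anesthesia" and "Intraoperative TEAS group: From 30 min before anesthesia to the end of surgery", each a single session. The postoperative arm has a daily session for seven days. The pre- and postoperative arm is treated thus: "From 1 day before the operation until 7 days after, once daily in the morning". The perioperative arm has a session on the day before surgery, one running through surgery, and one on each of the first three days afterwards. Sham follows the perioperative arm's electrode placement without current.

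**The concern.** The trial asks which TEAS schedule is best, and safety is part of that answer. A capture window attached to each session makes observation time a function of the schedule itself. A higher event percentage in a long-schedule arm could then mean that the schedule does more harm, or only that it was watched for longer.

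Restricting the record to treatment-related events would remove the problem if relatedness could be judged without error. Several of the listed events also occur after gastrointestinal resection without any stimulation, and most windows fall in the days after surgery. The natural check on attribution is the frequency of the same events in patients who had no electrodes, but the stated rule gives control patients no window. At stake is the fair reading of the safety comparison between arms.

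**Working it through.** **Denominator.** The article's group size reproduces: (1.96 + 1.282)² × 2 × 2.35² / 2.0² = 29.02; × 1.3 = 37.73, rounded up to 38; 7 × 38 = 266. The article gives no adverse event rate to reproduce.

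**Windows per arm**, counted from the Intervention section:

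| Arm | Count | Windows |
|---|---|---|
| Control | none | 0 |
| Preoperative | 1 | 1 |
| Intraoperative | 1 | 1 |
| Perioperative | 1 + 1 + 3 | 5 |
| Sham | as perioperative | 5 |
| Postoperative | 7 | 7 |
| Pre- and postoperative | 1 + 7, or 1 + 1 + 7 if the day of surgery counts | 8 or 9 |

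**Model.** Suppose TEAS causes no events. Let b be the chance of a background event in one window and m the share of such events that is classed as treatment-related. The recorded rate per window is q = b × m. With k windows and a constant, independent q, the share of patients with at least one recorded event is 1 − (1 − q)^k. Neither b nor m is in the article, so q is an assumption and a range is shown.

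| Windows | q = 0.5% | q = 1% | q = 2% | Expected patients of 38 at q = 1% |
|---|---|---|---|---|
| 0 | 0 | 0 | 0 | 0 |
| 1 | 0.5% | 1.0% | 2.0% | 0.4 |
| 5 | 2.5% | 4.9% | 9.6% | 1.9 |
| 7 | 3.4% | 6.8% | 13.2% | 2.6 |
| 8 | 3.9% | 7.7% | 14.9% | 2.9 |
| 9 | 4.4% | 8.6% | 16.6% | 3.3 |

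Example: 1 − 0.99⁸ = 7.7%, and 38 × 0.077 = 2.9 patients.

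**Reading.**
- Perioperative and sham share 5 windows, so at any q their expected background shares are equal (4.9% each at 1%) and that contrast is fair.
- Preoperative against pre- and postoperative is not: 1.0% against 7.7-8.6% at q = 1%, with no effect of TEAS.
- Control is zero by construction, so it says nothing about b.
- If attribution is perfect, m = 0, so q = 0 and every entry is zero.

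**Limit of the model.** A constant q is a simplification. The window that starts on the day before surgery lies largely before the operation, while the single window of the preoperative and intraoperative arms takes in the first hours after it. The real gradient may be flatter or steeper than the table. The unequal number of windows does not depend on the model.

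**The case against.** The strongest reply is that the article counts only treatment-related events. An untreated patient cannot have one, so zero windows in control follows from the definition, and the table matters only if background events are misclassified. This stands as a limit on size: the documents support no particular q. It does not remove the point, because the article gives no way of separating vomiting or pain due to the operation from vomiting or pain due to TEAS, and the arm that could show the background rate has no capture.

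A per-treatment window can also be defended as an exposure-based choice if rates are given per session. That would correct for the number of windows if the background were constant, but it would still leave control unobserved and would still mix windows at different distances from surgery.

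Three stronger readings are tempting, and the documents do not support them.

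- *There is no comparator at all.* Sham matches the perioperative arm. Pain scores are also collected before surgery and on day 3 with no restriction by arm, so pain has some control-arm data. Neither covers the arms with 1, 7 or 8-9 sessions for the whole list of events.
- *Capture is expressly confined to 24 h, and relatedness is judged unblinded.* Both are inferences. The confinement follows only because no other window is stated, and the 24 h phrase could attach to the last listed item alone. The article does not say who judges relatedness or who is blinded. Even on the narrower grammatical reading, control has no stated capture.
- *The 5% rule is unusable, or will fire on surgical background.* Its unit and denominator are details that an article may leave to the full protocol. A forecast also depends on unknown inputs. With one common share of patients having a counted background event, the chance of 2 or more of 38 is 6% at a share of 1%, 18% at 2%, 57% at 5% and 90% at 10%. The chance of 12 or more of the 228 patients with electrodes runs from practically nil at 1% through 0.2% and 47% to 99.7%. The documents do not favour any of these.

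**Conclusion.** The point holds in a limited form. The rule as written gives the arms between 0 and 8-9 observation windows, and only the perioperative arm has a comparator with the same number. Event percentages by arm will therefore differ with schedule length to the extent that background surgical events are attributed to TEAS. At an assumed 1% per window the spread among treated arms is about 1% to 8-9% of patients; at 0.5% it is 0.5% to 3.9-4.4%; at 2% it is 2% to 14.9-16.6%. These figures rest on a constant, independent rate per window and on no TEAS effect, and they fall to zero with perfect attribution. The finding concerns safety ascertainment alone and has no bearing on the primary outcome or the sample size.

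**What to change.** Record the listed events, whether or not judged related to TEAS, on the same form in all seven arms over one common period: from the day before surgery to 24 h after the time of the day-7 session, or the corresponding time in arms without that session. Where a patient is discharged earlier, use self-report, which the Safety analysis section already allows. Report the number and percentage of patients with at least one event by arm, alongside control and sham. Keep the treatment-related count within 24 h of a session as a secondary display, so the information now planned is not lost.

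Leave the 5% rule and its threshold unchanged. Reading it against the control or sham rate would turn an absolute safety trigger into a relative one, which is not proposed here.

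The cost is a modest amount of extra data collection, mainly in the control and short-schedule arms and after any early discharge; the article does not give discharge timing, so that part cannot be sized. The change is best made before enrolment, because events that were never asked about in control patients cannot be reliably recovered later.

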### Outcome measures

#### Main outcome

The primary outcome of this study will be the change in cognition. The neuropsychological test will be measured preoperatively and 3 days postoperatively. Telephone Interviews for Cognitive Status-Modified (TICS-m) will be measured 1, 3, and 6 months after the operation.

The neuropsychological test includes the Mini-Mental State Examination (MMSE), Auditory Verbal Learning Test-HuaShan version (AVLT-H), Digital Symbol Coding (DSC), Verbal Fluency Test (VFT), and Clock Drawing Task (CDT). These assessments will be conducted by experienced researchers who have received training in neuropsychological assessment. Postoperative cognitive dysfunction (POCD) is defined as occurring when two or more Test *Z*-values or the *Z*-total exceed 1.96, according to the “Z-score method” (31).

The MMSE is a widely used tool for detecting cognitive impairment in both clinical and research settings (32). This 30-point questionnaire evaluates various cognitive domains, including orientation (time and place), memory (immediate and short-term), attention, calculation, and language (naming, repetition, listening, reading, and writing) (33). A higher score indicates better cognitive function.

AVLT-H has been shown to be acceptable to Mandarin speakers and is sensitive to detecting amnestic mild cognitive impairment (aMCI) (34). It assesses memory by requiring patients to learn and recall a set of 12 words. Due to the knowledge and cooperation levels of the local elderly subjects, we will record their fourth recall, with each correctly recalled word earning 1 point (35).

DSC assesses executive function. In this test, subjects are required to match numbers with corresponding symbols within 90 s. Each correctly matched number earns 1 point (36). This test is a valid and reliable measure for detecting early signs of cognitive decline (37) and predicting cognitive disorders (38).

VFT primarily assesses language ability but also requires the integration of several cognitive functions, including speed, attention, inhibition, and self-monitoring (39). Although the task is relatively simple, it reflects the effective coordination of these functions (40). In the test, subjects are instructed to name as many animals, fruits, and vegetables as they can within 1 min. Each correctly named item earns 1 point, and repeated items receive no points (41).

CDT is a sensitive and specific measure for cognitive impairment (42) that evaluates visual–spatial structural ability. In this test, subjects are required to draw the dial of a clock on paper and correctly place the numbers in their respective positions. Scoring is as follows: ① Drawing a closed circular outline earns 1 point. ② Displaying the correct numbers in the proper sequence on the dial earns 2 points. ③ Positioning the hour and minute hands correctly earns 1 point. The test times are 08:10 (pre-) and 07:50 (post-) (43).

TICS-m is modeled after the MMSE and comprises 21 items categorized into three dimensions, with a total score of 50 points: memory (20 points), orientation (13 points), and language and attention (17 points) (44). A score of <28 points is indicative of dementia, while a score of 28–32 points is considered mild cognitive impairment (MCI). TICS-m has demonstrated good reliability and validity in the Chinese population (39).

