**Methods:**

A total of 266 geriatric patients who underwent radical resection of gastrointestinal tumors will be divided into seven groups: one control group (receiving standardized perioperative management), one sham intervention group (receiving TEAS treatment without electrical stimulation), and five intervention groups (receiving TEAS at different time intervals). The intervention groups will receive TEAS at bilateral Neiguan (PC6) and Zusanli (ST36) acupoints. The TEAS treatment will employ an altered frequency of 2/100 Hz with disperse-dense waveforms and an adjustable intensity, ensuring the stimulation remains below 10 mA and within a tolerable range for the patient. The device will output an asymmetrical biphasic pulse wave, with a pulse width of 0.2 ms ± 30%, based on electromagnetic compatibility basic performance testing. The primary outcome will assess changes in cognition, measured using neuropsychological tests administered preoperatively and 3 days postoperatively, as well as the Telephone Interview for Cognitive Status-Modified (TICS-m) at 1, 3, and 6 months postoperatively. Secondary outcomes will include preoperative and 3-day postoperative measurements of interleukin-6 (IL-6), S100 calcium-binding protein β (S100β), tumor necrosis factor alpha (TNF-*α*), insulin-like growth factor 1 (IGF-1), and C-reactive protein (CRP). Additional data will be collected on the time to postoperative exhaust, defecation, eating, and the first postoperative ambulation. Numeric Rating Scale (NRS) scores will be recorded before and on the third day after the operation, alongside Activities of Daily Living (ADL) and Braden scale scores, which will be assessed before the operation and at the time of discharge.

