### Patient population and setting

The equation for sample size calculation, *n* = (Z*
_α/2_
* + Z*
_β_
*)^2^ × 2*σ*^2^/δ^2^ where σ represents the average score of the Mini-Mental State Examination (MMSE) evaluated on the third day after the operation between the two groups. Based on previous pre-experimental data, this study employs a two-sided test with *α* = 0.05 and a test efficiency of (1-β) = 0.9, resulting in Z_α/2_ = 1.96, Z_β_ = 1.282. *σ* denotes the standard deviation, while *δ* represents the mean difference of MMSE scores on the third day after the operation between the intervention and control groups. According to the pre-experiment results, σ is 2.35, δ is 2.0, and considering a 30% increase in the sample size, each group requires 38 patients. Therefore, a total of 266 patients will be sequentially enrolled after meeting the eligibility criteria, with the attending doctor informing each patient and obtaining their informed consent. This study adheres to the principles of the Declaration of Helsinki.

To expand our pool of research subjects, we will promote recruitment on the hospital’s official account. Throughout the intervention, patients will retain the final decision-making authority regarding their participation in the trial.

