### Statistical analysis

All data will be analyzed using IBM SPSS software version 24.0. Research data following a normal distribution and expressed as x̄± SD will be analyzed using analysis of variance (ANOVA). For non-normally distributed data expressed as median (interquartile range), the Kruskal-Wallis H test will be applied. Categorical variables, presented as frequency (f) and percentages (%), will be analyzed using the chi-squared test and Fisher’s exact test as appropriate. Multiple imputation methods will be employed to handle missing data.

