## Discussion

Research has shown that the timing of TEAS interventions—whether administered 10–30 min preoperatively, throughout the entire surgical procedure, or solely preoperatively versus a combination of preoperative and postoperative treatment—can significantly improve cognitive function (12–14). Extended use of TEAS may lead to a “tolerance effect,” potentially diminishing its efficacy over time (19). Consequently, this protocol aims to investigate the optimal timing for TEAS to improve postoperative recovery in elderly patients. The results are expected to assist clinicians in formulating more effective perioperative management strategies, reducing the incidence of POCD, and enhancing postoperative cognitive function and quality of life for elderly patients.

Additionally, given the potential for a “tolerance effect” associated with prolonged TEAS use, it is essential to examine how varying intervention durations at different timings might influence this phenomenon. Future research should evaluate the impact of different intervention durations at these timings to ensure the sustained efficacy and safety of TEAS. Furthermore, exploring the effects of TEAS across diverse surgical procedures and patient subgroups will contribute to validating its generalizability and applicability. Further studies are needed to confirm the long-term effects and safety of TEAS to establish its reliability in clinical practice.

This study has several notable strengths. Firstly, it is the pioneering investigation into the effects of different TEAS timings on the postoperative recovery of elderly patients with gastrointestinal tumors, as previously mentioned. Second, we assessed the long-term cognitive function. Many studies have discussed TEAS in the short term, for example, in the third and seventh days after the operation (32, 45). However, POCD can last for months or years, and we investigated the cognitive function of patients 1, 3, and 6 months postoperative (6).

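### Eight or nine unranked variables are all primary, the trial is sized on one of them, and the only stated tests are seven-group omnibus tests that cannot by themselves show which timing is best

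*Protocol article*

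**What the plan says.** **Primary outcome (Main outcome).** "The primary outcome of this study will be the change in cognition". Three sets of variables stand under this heading:

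- A battery given before surgery and on day 3, whose fifth member is a clock-drawing test: "The neuropsychological test includes the Mini-Mental State Examination (MMSE), Auditory Verbal Learning Test-HuaShan version (AVLT-H), Digital Symbol Coding (DSC), Verbal Fluency Test (VFT), and Clock".
- A telephone scale: "Telephone Interviews for Cognitive Status-Modified (TICS-m) will be measured 1, 3, and 6 months after the operation".
- A binary classification: "Postoperative cognitive dysfunction (POCD) is defined as occurring when two or more Test" Z-values, or the Z-total, pass 1.96.

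No variable or time point is put first. Biomarkers and recovery measures have their own Secondary outcome section, so the division into primary and secondary was deliberate.

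**Sizing (Patient population and setting).** The target difference is the "mean difference of MMSE scores on the third day after the operation between the intervention and control groups". It is 2.0 with SD 2.35, two-sided alpha 0.05 and power 0.9. With a 30% increase this gives 38 per group.

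**Analysis (Statistical analysis).** Normally distributed data "will be analyzed using analysis of variance (ANOVA"), other continuous data go to Kruskal-Wallis, and categorical data go to chi-squared or Fisher tests. Patients "will be divided into seven groups" (Abstract, Methods): control, sham and five TEAS schedules.

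**Aim (Discussion).** "this protocol aims to investigate the optimal timing for TEAS to improve postoperative recovery in elderly patients".

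**The concern.** Three parts of the article describe three different trials. The outcome section describes a trial with many primary variables. The sizing describes a two-group trial on one variable. The analysis describes a seven-group global test. The aim, choosing among five timings, is a fourth question.

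Two things are at stake. First, with no variable ranked, the trial could report success on its primary outcome from any one of eight or nine results, each tested at 5%. Second, a significant seven-group test says only that the means are not all equal. Because sham and control are among the seven, the result may come entirely from control differing from everyone else, and then it says nothing about timing.

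**Working it through.** **1. The plan's own figure.** Inputs from Patient population and setting: Z values 1.96 and 1.282, SD 2.35, difference 2.0, increase 30%.

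n = (1.96 + 1.282)² × 2 × 2.35² / 2.0² = 29.02. Then 29.02 × 1.3 = 37.7, so 38 per group, and 7 × 38 = 266. The arithmetic reproduces. It buys 90% power for one unadjusted two-group comparison on day-3 MMSE with about 29 evaluable per group.

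**2. Count of primary variables.** Five day-3 tests + three TICS-m assessments = 8. Adding POCD gives 9. The three TICS-m values have no preoperative counterpart, as the Discussion concedes, so they cannot express a change from baseline.

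**3. False positives over the omnibus tests.** Assumptions: no true effect, each variable tested at 0.05, success on any one counts.

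- Independent variables: 1 − 0.95⁹ = 0.370; 1 − 0.95⁸ = 0.337.
- Equally correlated variables (the correlation is assumed; the documents give none), simulated as seven-group ANOVA with 38 per group, 4,000 runs, all variables treated as continuous:

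| Correlation | 8 variables | 9 variables |
|---|---|---|
| 0 | 34% | 37% |
| 0.3 | 31% | 33% |
| 0.5 | 27% | 29% |
| 0.7 | 21% | 21% |

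Independence cannot hold. POCD is computed from the same five tests, and TICS-m is one scale repeated three times. So 37% is an upper bound.

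**4. What a significant omnibus test tells.** Noncentrality is λ = n Σ(μᵢ − μ̄)² / σ², with n = 38 and σ² = 2.35² = 5.5225.

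- All five timings 2.0 above sham and control: Σ = 5 × 0.571² + 2 × 1.429² = 5.71; λ = 38 × 5.71 / 5.5225 = 39.3; power 99.9%.
- Only one timing 2.0 above the other six groups: Σ = 1.714² + 6 × 0.286² = 3.43; λ = 23.6; power 97%.
- Only control 2.0 below the other six groups: the same Σ, so again 97%.

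The test is nearly certain to be significant in all three cases. In the first and third no timing is better than another.

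**5. Power once contrasts are stated.** Each contrast has noncentrality δ / (2.35 × √(2/n)). For δ = 2.0 this is 3.24 at n = 29 and 3.71 at n = 38. Two-sided critical values with the seven-group error variance are about 2.53 (Dunnett, five groups against control) and 2.75 (Tukey, five groups).

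| Contrast | 29 evaluable per group | 38 evaluable per group |
|---|---|---|
| TEAS vs control, 2.0 points (Dunnett) | 76% | 88% |
| Timing vs timing, 2.0 points (Tukey) | 69% | 83% |
| Timing vs timing, 1.0 point (Tukey) | 13% | 19% |

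The 1.0-point row is an assumption: two active schedules may well differ by less than active differs from control. As a rough guide with Bonferroni, 90% power at 2.0 points needs 42 evaluable per group for five contrasts (42 × 1.3 gives 55; 55 × 7 = 385). For ten contrasts it needs 47 (47 × 1.3 gives 62; 62 × 7 = 434).

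**The case against.** The strongest reply is that this is a condensed article with a one-paragraph statistics section. Contrasts, post hoc procedures and multiplicity rules are commonly left to a full protocol or SAP, and neither is shown. That stands: their absence alone is no finding, and the section does not say that the analysis stops at the omnibus test. It does not answer the conflict between a multi-variable primary outcome and single-variable sizing, because both are stated in the article.

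Three stronger readings are tempting and are not supported.

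- **Unadjusted pairwise testing.** A reader might infer that unadjusted pairwise tests will follow. On one variable these would give about 44% false positives over all 21 pairs, or 28% over the ten pairs of TEAS groups, and more still over all variables. No section plans such tests, so these rates do not describe this plan.
- **The aim is out of reach.** A reader might infer that the trial cannot identify a best timing. What can be said is that the tests stated here do not do so by themselves; suitable contrasts on the same data could.
- **Timing is separable from amount.** The Intervention section gives schedules that differ in number and length of sessions, and a reader might hope to isolate timing from nested pairs of arms. Every such pair also adds stimulation time, and perioperative minus intraoperative adds sessions both before and after surgery. Comparing whole schedules is still a legitimate question. The Abstract speaks of timing strategies, and the Discussion leaves duration to later research. Only the label on the result needs care.

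**Conclusion.** The concern holds in this form: the article makes eight or nine variables primary without ranking them, sizes one of them for one two-group comparison, and states only omnibus tests for a trial meant to choose among timings. The chance of at least one false-positive omnibus result is about 21% to 37%. That range assumes that success on any variable counts, which the document neither says nor rules out, and that correlations lie between 0.7 and 0. The sample size arithmetic itself is correct. The outcome and sizing conflict does not depend on an unseen SAP. The missing contrasts matter because the aim needs them, but their absence from the article is not counted as an error. The point should be settled before any comparative data are seen, since it decides what the trial can conclude.

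**What to change.** 1. **Name one primary variable and time point.** Day-3 MMSE matches the sizing. If another is chosen, justify it and redo the sizing. In either case note that the two seven-day postoperative schedules in the Intervention section are incomplete at day 3, so a day-3 comparison reflects only part of them.
2. **Make the other variables secondary**: the remaining day-3 tests, POCD and TICS-m at 1, 3 and 6 months.
3. **Replace the omnibus test for the primary variable** by one linear model with an ordered set of contrasts under a single overall 5% level. For example, test each TEAS group against control first (Dunnett), then all pairs among the five TEAS groups (Tukey). Use the confidence intervals from the second step as the basis for any claim that a timing is optimal. State the rule for passing from the first family to the second. Treat perioperative TEAS against sham, the only schedule-matched sham comparison, as supportive. Testing the three families at 5% each, with no order, would leave about 13% overall error under no effect (simulated), so the ordering matters.
4. **Report between-arm differences as differences between regimens**, because the arms differ in amount of stimulation as well as in timing.

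The cost is fewer primary outcomes, wider intervals and lower power, and the plan should say so. The 76% and 69% (29 per group) or 88% and 83% (38 per group) for 2.0 points are per contrast; a gate between the families lowers the second figure of each pair further. At 13% to 19% power for a 1.0-point difference between timings, a non-significant comparison cannot be read as equivalence.
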